### Data analysis

Characteristics of the study sample will be described, using frequencies of participants and non-participants after two-year follow-up. Possible (selective) differences between the completers and non-completers will be tested using chi-square test for categorical variables and t-test for continuous variables. The course of trauma-related and personality disorders will be determined by comparing the two-year follow-up outcome with the baseline diagnostic status on four variables. For the categorical variables, i.e. presence of PTSD diagnosis (yes/no) and presence of a personality disorder (yes/no), we use chi-square statistics. For the continuous variables, i.e. severity score on the CAPS for PTSD (range 0–144) and total number of criteria met for personality disorders et cetera, we use analysis of variance. We will use a Bonferroni correction for multiple testing.

The aim of the current study is to validate the model of Draijer as a prognostic model. For an extensive description of this model and the validation of the model as a diagnostic instrument, we refer to [23]. In short, two severity indexes will be constructed, one for traumatization and one for neglect, to test relationship between the severity of chronic childhood trauma and neglect, and the severity of respectively trauma-related disorders and personality disorders. We test the possibility of relating the diagnostic square to changeability of psychopathology within a period of 2 year, by using a changeability score, based on the sum of the two severity indexes at baseline (range 0–10), as a predictor in a regression analysis on the raw difference scores (i.e. CAPS-score at follow-up minus CAPS-score at baseline). In addition, the changeability score can be replaced by separate scores on severity of traumatization and severity of neglect, so we can compare the regression coefficients and test if both axis of the square are equally related to the observed change after 2 years.

Secondly, to find determinants (predictors) of the two-year course, we will use logistic regression analysis for dichotomous primary outcome measures, as descripted in the power calculation. Again, we will use a Bonferroni correction for multiple testing. The amount of predictors we will test, will be based on literature and the distribution of our data.

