### Participants

Patients who sought treatment at GGZ Friesland for either personality disorders or trauma-related disorders were recruited for the baseline data collection. Baseline data were collected between November 2011 and March 2014. The inclusion period of the follow-up assessment runs from February 2014 until August 2016. All patients who completed baseline assessment will be invited to participate in the follow-up study, 2 years after they completed the baseline assessment. This includes 150 patients (116 women and 34 men): 49 patients who sought treatment for traumatic experiences and were admitted to a specialized trauma-related disorders treatment program, aimed specifically at adult survivors of prolonged early childhood trauma, and 101 patients who sought treatment for personality pathology and were consecutively referred to a specialized personality disorders treatment program. For a detailed description of the inclusion at baseline, we refer to [23]. Only participants with insufficient mastery of the Dutch language were excluded. Data on non-response as well as representativeness of the baseline sample are presented elsewhere [23]. The baseline sample was considered to represent the two relevant clinical populations.

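### The two yes/no diagnoses are compared within patients over two years, but the plan names only chi-square, which on its ordinary reading does not properly test paired change

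*Protocol article*

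**What the plan says.** The Participants section makes the design paired: "All patients who completed baseline assessment will be invited to participate in the follow-up study, 2 years after they completed the baseline assessment". The Data analysis section builds the primary comparison on that pairing: "The course of trauma-related and personality disorders will be determined by comparing the two-year follow-up outcome with the baseline diagnostic status on four variables".

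Two of the four variables are binary, and for these: "For the categorical variables, i.e. presence of PTSD diagnosis (yes/no) and presence of a personality disorder (yes/no), we use chi-square statistics". The other two are the CAPS severity score and the count of personality disorder criteria; that sentence ends "total number of criteria met for personality disorders et cetera, we use analysis of variance". Then: "We will use a Bonferroni correction for multiple testing". The divisor is not given. No McNemar test, paired test or within-subject factor is mentioned.

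Just before this, the same section uses chi-square for two groups that really are independent: "Possible (selective) differences between the completers and non-completers will be tested using chi-square test for categorical variables and t-test for continuous variables".

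Later in the section, the raw follow-up-minus-baseline CAPS difference is regressed on the severity indexes. That is a within-patient analysis, but it asks what predicts change, not whether change occurred.

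**The concern.** Each patient contributes a baseline and a two-year diagnosis, so the evidence on change lies in the patients whose status differs between the waves: those who remit and those who are newly diagnosed. An ordinary chi-square does not use the data that way. It can be applied in two ways.

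- **Cross-table.** Baseline status against follow-up status. The null hypothesis is that the two are unrelated. For disorders that persist, that null is usually false whether or not prevalence has moved, so a significant result would be read as a finding about course when it may only show that diagnosis is stable.
- **Stacked waves.** Baseline prevalence against follow-up prevalence, as if from different people. The right quantity is compared, but the standard error ignores the positive correlation within patients and is too large, so a real fall can be missed.

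The same question arises for analysis of variance on the two scores if it is run between groups. At stake is the test result for the primary research question.

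**Working it through.** **The plan's own figures.** Ten events per variable at 25% (or 75%) remission gives 10 / 0.25 = 40 patients per predictor. Three predictors give 3 × 40 = 120, and 20% drop-out gives 120 / 0.80 = 150. Both stated numbers reproduce. They rest on the logistic regression alone; no power is stated for the baseline versus follow-up tests.

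**Inputs.** From the article: n = 120 pairs expected at follow-up. Assumed, because the article gives none: prevalences, within-patient correlation (phi or r), effect size, and a Bonferroni divisor of 4 (alpha 0.05 / 4 = 0.0125).

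**Notation.** a = diagnosed at both waves, b = baseline only, c = follow-up only, d = neither.

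- Cross-table chi-square = n(ad − bc)² / [(a+b)(c+d)(a+c)(b+d)]
- Stacked chi-square = (p₁ − p₂)² / [p̄(1 − p̄) × 2/n], with p₁ = (a+b)/n, p₂ = (a+c)/n and p̄ their mean
- McNemar = (b − c)² / (b + c)

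**Step 1: worked tables, n = 120.**

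| a/b/c/d | Prevalence | Cross-table | Stacked | McNemar |
|---|---|---|---|---|
| 45/15/15/45 | 50% to 50% | 30.0 (p = 4×10⁻⁸) | 0 (p = 1) | 0 (p = 1) |
| 24/56/12/28 | 66.7% to 30% | 0 (p = 1) | 32.3 (p = 1×10⁻⁸) | 28.5 (p = 1×10⁻⁷) |
| 40/20/5/55 | 50% to 37.5% | 43.6 (p = 4×10⁻¹¹) | 3.81 (p = 0.051) | 9.0 (p = 0.0027) |

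Row 1, cross-table: 120 × (2025 − 225)² / 60⁴ = 388,800,000 / 12,960,000 = 30.0. McNemar: (15 − 15)² / 30 = 0. There is no net change, yet chi-square is overwhelming.

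Row 2, cross-table: ad − bc = 672 − 672 = 0. There is a large fall, yet chi-square is nil.

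Row 3, McNemar: (20 − 5)² / 25 = 9.0. Stacked: 0.125² / (0.4375 × 0.5625 × 2/120) = 0.015625 / 0.004102 = 3.81. The pairing decides the result.

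Rows 1 and 2 need no assumption about effect size or correlation: the cross-table tests a different hypothesis.

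**Step 2: error rate with no change** (60% at both waves, nominal 5%, simulated).

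| phi | Cross-table rejects | Stacked rejects | McNemar rejects |
|---|---|---|---|
| 0 | 5% | 5% | 5% |
| 0.3 | 91% | 2.0% | 5% |
| 0.5 | 100% | 0.6% | 5% |
| 0.7 | 100% | 0.1% | 5% |

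**Step 3: power of the stacked form against McNemar** (60% to 45%, simulated).

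| phi | alpha 0.05: stacked / McNemar | alpha 0.0125: stacked / McNemar |
|---|---|---|
| 0 | 63% / 64% | 42% / 42% |
| 0.3 | 65% / 79% | 41% / 60% |
| 0.5 | 68% / 92% | 39% / 79% |
| 0.7 | 73% / 99.7% | 36% / 98.5% |

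**Step 4: continuous scores.** In SD units, the variance of the mean change is 2(1 − r)/n when paired; a between-groups analysis uses 2/n. For a change of 0.30 SD at alpha 0.05, power between-groups / paired is 64% / 64% at r = 0, 67% / 79% at 0.3, 70% / 91% at 0.5 and 75% / 99% at 0.7. Repeated-measures ANOVA with two waves is the paired t-test, so under that reading nothing is lost.

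**The case against.** The strongest reply is that the named methods include the right ones. McNemar's statistic is referred to a chi-square distribution, and repeated-measures ANOVA is an analysis of variance. The authors clearly know the data are paired, since they also model difference scores. Their wording shifts too: for completers against non-completers they write of a t-test, and for baseline against follow-up of analysis of variance. A between-groups ANOVA on two waves is just that t-test, so the change of name hints at a repeated-measures design. A journal article may also leave the exact form to a fuller plan.

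For the continuous scores this stands. A reader might infer that the ANOVA is wrong, but the text does not say which form is meant and leans, if anything, towards the paired one.

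For the diagnoses it stands only in part. The paired reading cannot be excluded, but the section has just used chi-square for independent groups, and nothing tells the reader that the meaning has changed. The article is not silent here: it names a test for its primary question, and the ordinary form of that test does not answer it properly.

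A reader might also infer that the study loses much of its power. The documents do not support a flat statement. The loss applies only to the stacked reading and depends wholly on assumed inputs. The article expects 25% to 75% remission. With an assumed 60% baseline rate, 10% new onset among the rest and alpha 0.0125, stacked against McNemar power is 9% against 64% at 25% remission, 98% against 99.9% at 50%, and about 100% for both at 75%. The range runs from nil to large.

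**Conclusion.** The point holds for PTSD diagnosis and personality disorder diagnosis. On its ordinary reading the named test either addresses association instead of change, or compares the two prevalences with an error rate below nominal. The first fault does not depend on any assumed figure. The second is conditional: for 60% to 45%, n = 120 and alpha 0.05, the power loss is about nil at phi 0, 14 points at 0.3 and 24 points at 0.5, and the article gives no correlation from which to choose among these.

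For CAPS severity and the criteria counts the finding is an ambiguity only.

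It should not be carried over to the rest of the plan. The sample size of 120 and 150, the logistic regression of remission and the difference-score regression do not use these tests and are unaffected.

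**What to change.** In the Data analysis section, replace chi-square for the two diagnoses with McNemar's test. Report the change in prevalence with a paired confidence interval, and show the 2×2 transition table (persistent, remitted, newly diagnosed, never diagnosed). For the 40/20/5/55 table above, for example, the fall is 12.5 points with standard error √(25 − 15²/120) / 120 = 0.040, so the 95% interval is 12.5 ± 1.96 × 4.0, about 4.6 to 20.4 points.

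For CAPS severity and criteria counts, state that the analysis of variance is the repeated-measures form, or name a paired t-test, which is the same test with two waves. A mixed model is an option, not a requirement. Keep the Bonferroni correction.

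The cost is one or two sentences. No new data, patients or assessments are needed.

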Furthermore, to measure possible determinants of course outcome we collect data from the patient record system of GGZ Friesland, including score on the Global Assessment of Functioning (GAF) Scale, last reported clinical diagnosis and data on the received therapy during the follow-up period. Data on therapy will consist of doses (the amount of received therapy in minutes) and will be specified in treatment program/department (trauma-related or personality or other), group versus individual therapy, days of hospitalization and the use of medication. In case of treatment outside GGZ Friesland, patients are asked to fill in an additional form. This form contains questions on type and duration of treatment (s) received outside GGZ Friesland, number and duration of hospitalization outside GGZ Friesland and the use of medication (e.g. type, dose and duration), prescribed outside GGZ Friesland, in the two-year period after the baseline assessment. This information will be comparable to the data on therapy inside GGZ Friesland. In addition, data on treatment history before baseline is assessed with the STI [34].

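### The regressions meant to validate the prognostic model combine two separately recruited programme cohorts with no programme term, so a between-programme difference can look like an effect of trauma and neglect severity

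*Protocol article*

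**What the plan says.** Participants (protocol article) describes two groups that entered by different routes. The first group is "49 patients who sought treatment for traumatic experiences and were admitted to a specialized trauma-related disorders treatment program"; that programme is described as "aimed specifically at adult survivors of prolonged early childhood trauma". The second group, about twice as large, is "101 patients who sought treatment for personality pathology and were consecutively referred to a specialized personality disorders treatment program". The section adds: "The baseline sample was considered to represent the two relevant clinical populations".

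Data analysis sets out the validation test. The predictor is formed "by using a changeability score, based on the sum of the two severity indexes at baseline" (range 0 to 10) and is used "as a predictor in a regression analysis on the raw difference scores (i.e. CAPS-score at follow-up minus CAPS-score at baseline"). In a second version, "the changeability score can be replaced by separate scores on severity of traumatization and severity of neglect", so that the two coefficients can be compared and the axes tested for an equal relation to change. Neither version includes a programme term, a stratification or a within-programme analysis.

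Programme is recorded. Under Measurements, the therapy data "will be specified in treatment program/department (trauma-related or personality or other"). The one multivariable model spelled out under Power calculation is logistic. It holds treatment duration, trauma severity and neglect, but not programme.

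**The concern.** One programme selects on early trauma and the other on personality pathology, so the programmes may well differ on one or both severity indexes. The article itself expects the type of treatment to predict course (end of Background), and it tracks therapy as something that may alter symptoms (Discussion). The outcome is a PTSD scale, and only one of the two programmes is built around trauma. Programme may therefore be related to both the predictor and the outcome.

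In that case a single regression over all patients mixes two things: how change relates to severity among patients of the same programme, and how the two programmes differ on average. The second could be read as support for the trauma-and-neglect model, or as evidence that one axis matters more than the other, without any relation inside either programme. Validating the model prognostically is a stated aim, so the basis of that claim matters.

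**Working it through.** **The plan's own figures.** Ten events per variable at a 25% event rate (or 75%, where non-events are the rarer class) gives 10/0.25 = 40 patients per predictor. Three predictors need 3 x 40 = 120, and 20% drop-out gives 120/0.8 = 150. The cohorts add up: 49 + 101 = 150. All figures reproduce.

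**Inputs from the article.** Cohorts of 49 and 101; 120 analysed. In the same proportion, 120 x 49/150 = 39.2, so the split is taken as 39 and 81.

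**Assumed inputs.** The article gives neither the severity indexes nor CAPS change by programme. Let d be the programme gap in the severity score and g the gap in CAPS change, both in within-programme SDs. The within-programme effect of severity is set to exactly zero.

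**Spurious slope.** With q = 49 x 101/150² = 0.22, the pooled slope in SD units is q·d·g/(1 + q·d²). For d = g = 0.8 this is 0.22 x 0.64/(1 + 0.22 x 0.64) = 0.1408/1.1408 = 0.123.

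**False-positive rate of the sum score.** Simulation at N = 120, 20,000 runs per setting, two-sided 5% test:

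| d | g | Spurious slope | Without programme | With programme |
|---|---|---|---|---|
| 0 | 0.5 | 0 | 5.0% | 5.0% |
| 0.25 | 0.25 | 0.014 | 5.1% | 5.0% |
| 0.5 | 0.5 | 0.052 | 8.8% | 5.1% |
| 0.8 | 0.5 | 0.077 | 13.9% | 5.1% |
| 0.8 | 0.8 | 0.123 | 26.6% | 5.1% |
| 1.0 | 0.8 | 0.144 | 37.5% | 4.9% |

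**Separate-axes model.** 4,000 runs per setting, g = 0.5, the two indexes independent within programme, no programme term:

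| Trauma gap | Neglect gap | Sum score | Trauma coefficient | Equal-axes test |
|---|---|---|---|---|
| +0.8 | 0 | 10.5% | 15.0% | 9.5% |
| +0.8 | -0.8 | 4.9% | 12.1% | 22.1% |
| +0.8 | +0.8 | 21.5% | 10.8% | 5.2% |

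Opposite gaps cancel in the sum, and the distortion moves to the comparison of the axes. Gaps in the same direction do the reverse.

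**Programme as a fourth predictor in the logistic model.** By the plan's own rule this needs 4 x 40 = 160 analysed and 160/0.8 = 200 at baseline. With 120 analysed and 25% remission it leaves 120 x 0.25/4 = 7.5 events per variable.

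**The case against.** **The gaps are unknown, and may cancel.** A reader might infer that programme is tied by design to the severity score, and so that the sum score is certainly biased. The article does not support that. It reports no index or CAPS value by programme. Its own model links trauma to trauma-related disorders and neglect to personality disorders, so one programme could be higher on each axis and the sum could be nearly equal. This objection stands for the sum score. It does not protect the equal-axes comparison, although the article words that analysis as an option.

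**Programme is partly a consequence of trauma.** Patients entered the trauma programme because they sought help for traumatic experiences, and programme then shapes treatment. Adjustment can remove part of a real effect and narrows the range on the trauma axis. A score that predicts partly through referral still predicts. A reader might nevertheless want the within-programme slope to be the sole evidence. That goes too far: it would change the question asked, since the square is meant to locate every patient.

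**Programme in every regression is not cheap.** This stands for the logistic model, where a fourth predictor breaks the plan's own rule.

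**The predictor list is open.** Data analysis leaves the number of predictors to the literature and the data, and programme is recorded. That sentence, however, belongs to the logistic models. For the CAPS-change regression the predictor, the outcome and the variant are all stated.

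**The mix of 49 and 101 is not an error.** A reader might fault the combined sample as no natural population. The article claims only that it represents two populations.

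**Even in the worst case tabulated, most studies would not reach significance** (37.5% at d = 1.0, g = 0.8). That is true, but it is still far above 5%.

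**Conclusion.** The point holds in a conditional form. As stated, the CAPS-change regressions cannot separate a severity effect from a difference between programmes. For the sum score, the false-positive rate ranges from nominal (no gap in the sum, or both gaps 0.25 SD), through about 9% (both 0.5 SD), to about 27% (both 0.8 SD). With opposite axis gaps of 0.8 SD and a 0.5 SD gap in change, the sum stays at about 5% while the equal-axes test is at about 22%. A programme term brings the sum-score rate to between 4.9% and 5.2% in every setting simulated.

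These figures rest on assumed gaps, a zero within-programme effect, normal data and one 5% test. A Bonferroni-corrected level would lower the absolute rates without removing the inflation. The conclusion is that the validation claim is exposed, not that it will be wrong. This is a worthwhile, inexpensive improvement.

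**What to change.** - In the linear CAPS-change regressions (sum score and separate axes), fit each model with and without intake programme and report both slopes side by side.
- Show the results by programme and the index-by-programme interaction as a check.
- Claim validation of the trauma-and-neglect model only if the association is not merely a between-programme difference.
- In the three-predictor logistic model, use programme in a sensitivity analysis only.

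The cost is one degree of freedom for the programme term in the linear models, using a variable already known for every patient; the interaction check takes a little more. The drawback is that the adjusted slope may understate a real effect, because programme partly follows from trauma history and determines treatment. It should be read together with the unadjusted slope and should not replace it.

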Although many studies have focused on describing the comorbidity between trauma, trauma-related disorders and personality disorders [23], little research has been done on the long term course of these comorbidities. This lack of information is due to methodological limitations of previous studies, like short term follow-up [7, 14], using only (self-report) symptom questionnaires [10, 13, 15], and, concerning (comorbidity of) personality disorders, focussing only on specific disorders, like BPD [19, 20]. We designed the present study to overcome these limitations of the previous studies and expect therefore to be better able to identify predictors of two-year course outcome. Furthermore, the present study will test a theoretical model of Draijer [23, 24], while previous studies lack a theoretical background. We use the diagnostic square of Draijer (see Fig. 1) to study the (comorbid) course of trauma-related disorders and personality disorders. This two-dimensional diagnostic model accounts for the influence of trauma and neglect on the development of (the spectrum of) trauma-related disorders as well as personality disorders. The severity of trauma endured, as the first dimension, situated on the y-axis, fluctuates depending on factors such as the age on which the trauma occurred, how frequently it occurred and the relationship to the perpetrator. This dimension is assumed to be related to the severity of trauma-related disorders. Situated on the x-axis, the severity of emotional neglect represents the second dimension. This dimension is assumed to be related to the severity of personality disorders. Thus a square is created, that gives an indication on the treatability of these disorders by psychotherapy, with highly treatable psychopathology on the low end of the dimensions, and highly untreatable psychopathology on the high end of the dimensions [24]. While this model already has shown its relevance in clinical practice as a diagnostic model, the aim of this study is to test if it can be validated as a prognostic model for course of illness: will it be affected by characteristics of the patient, treatment (s) received and/or (the type and severity) of the (comorbid) symptoms of trauma-related and personality disorders.

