## Discussion

As with most follow-up (longitudinal) studies, the biggest challenge of this study is to reach all patients who participated in the baseline study [23]. Response rates in follow-up studies vary from 58% to 94% [2, 3, 14, 15, 22]. While the treatment of (complex) trauma-related disorders and personality disorders tend to take a long time, chances of patients still having therapy within GGZ Friesland are rather high. This makes it easier to contact patients and lowers the risk of expired telephone numbers and old addresses. However, while at baseline assessment was part of daily clinical routine for patients referred to trauma-related disorders program, the follow-up assessment is not embedded in any particular treatment program. This could lower the response rates. We expect non-response due to patients who are not able to participate (due to i.e. emigration, physical illness or death by suicide), patients who are not willing to participate (due to i.e. lack of time or motivation) and patients which cannot be reached (due to i.e. changed telephone numbers, changed addresses). To minimalize non-response during the study period, we keep in close touch with the treatment departments and treating clinicians. Furthermore, patients get well informed, we create a pleasant atmosphere during assessment and we concern (and anticipate on) the patients’ needs, as far as possible. All risks considered, we expect a non-response rate of 20%, leaving an N of 120. This N provides enough statistical power to answer the research questions.

Using the same psychologists to conduct the assessments at baseline and follow-up has both advantages and disadvantages. Psychologists must be well trained and have clinical expertise to obtain the clinical interviews in a reliable way. Psychologists meeting those criteria are scarce. The inter-rated agreement intervals were high at baseline (.90 to.95). Using other psychologist at follow-up can lower the inter-rated agreement. On the other hand, using the same psychologist can result in a bias towards a favourable course. However, we do not expect solitary favourable courses in our hypothesis. To minimalize any form of bias, psychologists are not allowed to look-up (individual) outcome at baseline, before they conduct follow-up assessment. Furthermore, we provide personal supervision by a senior clinical psychologist and encourage to reason the scoring of clinical interviews to enhance objectivity.

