We overcome limitations of previous studies, as discussed above, by using structured clinical interviews as well as symptom questionnaires, carefully registering onset and type of trauma (at baseline and follow-up) and collecting several data, which potentially act as predictors of course of disorders and symptoms. Furthermore, to keep track of factors that may affect symptom change, we enumerate use of medication, received therapy (in- and outside GGZ Friesland) and traumatic experiences in the two-year period after baseline assessment. Also, we keep track of developments, like changes in offered therapies in the specialized treatment programs (of trauma-related and personality disorders) at GGZ Friesland. However, we cannot overcome some limitations, inherent in this type of research, like the use of retrospective data. Also, in addition to the clinical interviews, we use some self-report questionnaires.

An important strength of this study is that it is unique in the elaborate way in which traumatization and (personality) pathology are investigated [23]. This study will provide insight in the relation between symptoms of trauma-related disorders and personality disorders and how they affect each other in the course of treatment, while they are frequently treated as separate conditions nowadays. Identifying factors, which influence the course of the trauma-related and personality disorders, allows making predictions about the future course and offers indicators for treatment. Furthermore, the study can contribute to improve diagnosing trauma-related disorders and personality disorders as well as provide knowledge of prognostic variables that may allow the prognosis of an individual patient and the pre-classification/stratification of patients in outcome studies.

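### The diagnostic square is to be validated as a prognostic model, but the analysis described for that aim tests association only, and at N = 120 a slope can be significant with an R² of about 3% to 6.5%

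*Protocol article*

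**What the plan says.** The Background states that "the aim of this study is to test if it can be validated as a prognostic model for course of illness". Data analysis repeats validation as a prognostic model as the study's aim and then says how it will be pursued: "We test the possibility of relating the diagnostic square to changeability of psychopathology within a period of 2 year".

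The predictor is a single changeability score, "based on the sum of the two severity indexes at baseline", with a range of 0 to 10. It is entered "as a predictor in a regression analysis on the raw difference scores", illustrated by follow-up CAPS minus baseline CAPS. No other covariate is named for this regression. In a second step the sum can be replaced by the two axis scores, to "test if both axis of the square are equally related to the observed change after 2 years".

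The Discussion lists among the study's possible contributions that it may "provide knowledge of prognostic variables that may allow the prognosis of an individual patient", and mentions pre-classification and stratification of patients in outcome studies. On sample size it says "we expect a non-response rate of 20%, leaving an N of 120", and that this number gives enough power for the research questions.

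**The concern.** A slope that differs from zero, or two axis slopes that do or do not differ from each other, is evidence about association. Validation of a prognostic model is a claim about prediction: how much of the variation in outcome the score accounts for, how large the error is for a single patient, and whether the score adds to what is already known at intake. Here the obvious comparator is baseline CAPS. It is already collected, and it is itself a component of the change score, so it will usually explain part of the change through regression to the mean.

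The article ties the stronger claim to the weaker analysis. If the plan is followed as described and the slope is significant, the natural sentence in the results paper is that the square has been validated as a prognostic model. The analysis cannot carry that sentence, because a very weak score can also give a significant slope.

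**Working it through.** **Inputs.** Baseline N = 150, 20% non-response and analysed N = 120 (Power calculation; Discussion). Response rates of 58% to 94% in other follow-up studies (Discussion). The significance level is not stated. I assume two-sided 0.05 and show results down to 0.005, which is 0.05/10, Bonferroni for ten tests. The article states Bonferroni for the course comparisons and for the logistic regressions, without a number of tests and not explicitly for this regression.

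**The plan's own figure.** Ten events per variable at a remission rate of 25%: 10/0.25 = 40 patients per predictor. Three predictors: 3 × 40 = 120. With 20% drop-out: 120/0.80 = 150. Both figures reproduce exactly. They were derived for the logistic regression on PTSD remission, not for the regression on CAPS change.

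**Smallest observed R² that is significant for one slope.** R² = t²/(t² + N − 2), with t the two-sided critical value on N − 2 degrees of freedom. At N = 120 and 0.05, t = 1.980, so R² = 3.921/(3.921 + 118) = 0.032 and r = 0.179 in absolute value. The residual SD relative to the SD of change is √(1 − R²) = √0.968 = 0.984, a reduction of 1.6%.

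| N | two-sided level | critical r (absolute) | R² | reduction in residual SD |
|---|---|---|---|---|
| 120 | 0.05 | 0.179 | 3.2% | 1.6% |
| 120 | 0.025 (2 tests) | 0.205 | 4.2% | 2.1% |
| 120 | 0.01 (5 tests) | 0.234 | 5.5% | 2.8% |
| 120 | 0.005 (10 tests) | 0.255 | 6.5% | 3.3% |
| 141 (94% of 150) | 0.05 | 0.165 | 2.7% | 1.4% |
| 87 (58% of 150) | 0.05 | 0.211 | 4.4% | 2.3% |
| 87 | 0.005 | 0.298 | 8.9% | 4.6% |

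**What this means for one patient.** The article gives no SD of CAPS change, so I express the result per 10 points of SD. Giving every patient the group mean leaves a 95% range of ±1.96 × 10 = ±19.6 points. At R² = 3.2% it is 19.6 × 0.984 = ±19.3, and at R² = 6.5% it is 19.6 × 0.967 = ±19.0. The figures scale in proportion to the true SD, and the percentage reduction does not depend on it. Error in the estimated coefficients is ignored, which flatters the score. Under bivariate normality (an assumption), r = 0.179 gives an AUC of about 0.58 for telling above-median from below-median change; 0.50 is chance.

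**How often a weak score gets through.** The R² values above are observed values at the boundary. For a score whose true R² is 3% (r = 0.173), Fisher's z gives atanh(0.173) × √117 = 1.89. Power is about Φ(1.89 − 1.96) = 47% at two-sided 0.05. Such a score could pass; it would not do so reliably.

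**The case against.** The strongest reply is that the article contains no rule saying that a significant slope counts as validation. A reader might infer one, since testing a relation is naturally read as testing a slope, but it is not written. That stands, so the point cannot be that a stated criterion is defective.

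A second reply is that explained variance, prediction error and internal validation are details that a condensed article may leave to the full protocol or analysis plan, and that R² is routine regression output. That also stands: their absence from the article is not itself a fault. What remains is what the article does say, namely that validation as a prognostic model is to be reached by relating a score to change and comparing two coefficients.

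Third, a reader might infer from the Discussion that the square is to be used for the prognosis of individual patients. The documents do not support this. The sentence is hedged, speaks of prognostic variables in general and does not name the square.

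Fourth, the sum-score regression is not the only look at the square's dimensions. The logistic regression for remission of PTSD includes severity of traumatic experiences and neglect along with duration of treatment. This is true, but it does not evaluate the sum score, and as described it too identifies predictors without assessing how well they predict.

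Finally, the aim can be read as a test of theory, and the Background's hypotheses are worded as relations between severity and improvement. For that aim a slope test is suitable. The word to change is then validation as a prognostic model.

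**Conclusion.** The concern holds as a mismatch between the stated aim and the analysis described for it. At the expected N of 120, a significant slope is compatible with an observed R² of 3.2% (two-sided 5%, no correction) to 6.5% (Bonferroni for ten tests), and so with a fall in residual SD of only 1.6% to 3.3%. Across the response range the article cites, the boundary at 5% runs from 2.7% to 4.4%; the least favourable case examined, N = 87 with ten tests, is 8.9%. In none of these does significance alone show useful prediction for a patient.

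The figures assume a simple linear regression with one predictor and a level that the article does not state. They describe what could happen at the boundary; the study may of course find a stronger relation. This is more than a question of missing detail, because following the described analysis could lead to a claim of validation that it cannot bear. It does not make the regression itself wrong as a test of association.

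**What to change.** In Data analysis, next to the regression on CAPS change:

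- Report R² with a 95% CI for the sum-score model and for the two-axis model.
- Report the increment in R² of each over a model with baseline CAPS alone.
- Report the prediction error in CAPS points.
- Correct these for optimism by bootstrap.
- Base any statement that the square is validated as a prognostic model on these results, preferably against a smallest worthwhile increment named before the follow-up data are analysed. Otherwise describe the result as an association with change.

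The cost is a few lines of text and some extra analysis. No new data are needed, since baseline CAPS is already collected. The drawback is that the claim of validation becomes harder to reach. If the investigators want only a test of the theory, the cheaper alternative is to word the aim as a test of association with two-year change.
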